# Online-group intervention after suicide bereavement through the use of webinars: study protocol for a randomized controlled trial

**DOI:** 10.1186/s13063-019-3891-5

**Published:** 2020-01-08

**Keywords:** Suicide bereavement, Grief, Group intervention, Webinar, Suicidality, Prolonged grief disorder, Randomized controlled trial

## Abstract

**Introduction:**

The death of a significant person through suicide is a very difficult experience and can have long-term impact on an individual’s psychosocial and physical functioning. However, there are only few studies that have examined the effects of interventions in suicide survivors. In the present study, we examine an online-group intervention for people bereaved by suicide using a group-webinar.

**Methods:**

The intervention was developed based on focus groups with the target group. The cognitive-behavioral 12-module webinar-based group intervention focuses on suicide bereavement-related themes such as feelings of guilt, stigmatization, meaning reconstruction and the relationship to the deceased. Further, the webinar includes testimonial videos and psychoeducation. The suicide survivors are randomized to the intervention or the waiting list in a group-cluster randomized controlled trial. Primary outcomes are suicidality (Beck Scale for Suicide Ideation) and depression (Beck Depression Inventory-II) and secondary outcomes are symptoms of prolonged grief disorder (Inventory of Complicated Grief-German Version ), posttraumatic stress disorder ( Revised Impact of Event Scale ), stigmatization (Stigma of Suicide and Suicide Survivor ) and posttraumatic cognitions (Posttraumatic Cognitions Inventory).

**Discussion:**

Previous studies of Internet-based interventions for the bereaved were based on writing interventions showing large treatment effects. Little is known about the use of webinars as group interventions. Advantages and challenges of this novel approach of psychological interventions will be discussed.

**Trial registration:**

German Clinical Trials Register, DRKS00014426. Registered on 12 April 2018.

**Protocol Version:**

3, 21.10.2019.

## Introduction

### Background and rationale

Global data showed that age-standardized mortality rates for suicide decreased by 32% worldwide between 1990 and 2016 [1]. However, suicide is still the leading cause of age-standardized years of lost life in the global burden of disease, specifically in high-income countries. The suicide of a significant person can leave a long-term impact on the surviving parent, child, partner, sibling or friend. While past research estimated about six individuals are affected by suicide [2], more recent studies reported much higher estimates, including not only the nuclear family, but also taking into account the social network of the deceased person. Berman [3] estimated that 45–60 people are intimately affected by suicide death, depending on the close daily or weekly contact the deceased person had with their social network.

Since 1989, the World Health Organization (WHO) has described people bereaved through suicide as a high-risk group for suicides and describes the aftercare of this group of victims as an essential part of national and international suicide prevention [4]. Suicide bereavement differs significantly in the grieving process from other circumstances of death. Typical reactions after a suicide are, in addition to normal grief reactions, the feeling of guilt and responsibility for the suicide, feeling of shame and rejection, low self-esteem, one’s own suicidal tendencies, the experience of stigmatization, and exposure to traumatic images [5]. Those affected often suffer lifelong functional impairment (e.g. inability to work, early retirement) as a result of suicide [6]. Kersting and colleagues [7] associated a higher risk of prolonged grief disorder in people bereaved by suicide (18.1%) or violent death (20%) compared with people responding to sudden but natural deaths. Furthermore, people bereaved by suicide report sleep disorders, somatic diseases (e.g. stomach ache, headache), and a significantly increased risk of being hospitalized [5, 8]. They are also more susceptible to crises [9]. In fact, more than half of the bereaved suffer depression and about 20% alcoholism, with the combination of the different disorders in particular having the highest suicide risk [10–14]. Pitman and colleagues [5], in their systematic review on mental health outcomes after suicide bereavement, noted increased admission to psychiatric care specifically in bereaved parents after a child’s death through suicide and an increased risk of depression in bereaved children after parental suicide.

Further, numerous population-based representative studies have demonstrated higher mortality after suicide compared to control groups. A Swedish epidemiological study of bereaved siblings (*N* = 160.588) showed that the brother or sister’s suicide in all age groups (18–69 years) had an up to 3.1 times higher mortality rate among the siblings than in non-sibling mourning control groups [15, 16]. Guldin and colleagues [17] investigated the consequences of the death of a parent in the first 18 years of life related to the suicidality of adult offspring (*N* = 7.302.033). The adult children had an 82% higher risk of suicidal death if a parent also committed suicide. Children who had a parent who died before they reached 6 years of age were specifically at higher risk to commit suicide themselves, and this risk remained high for at least 25 years [17]. Therefore, the suicide of a significant person does not only increase the risk of mental health disorders in the bereaved but they themselves also have an increased risk of death by suicide. For this reason, bereavement interventions aimed specifically at people who are bereaved by suicide play an important role in the aftercare.

### Interventions for suicide survivors

Interventions targeted at people bereaved by suicide are an important measure in the prevention of psychiatric illnesses and suicidal behavior. While self-help groups or counseling services for suicide survivors in the voluntary sector steadily increase, only a few psychotherapeutic interventions for survivors following suicide have been developed and have been scientifically evaluated. A recent systematic review included a total of 11 studies aimed at suicide bereavement; however, only a few of the included studies showed evidence of effectiveness in people suffering uncomplicated grief, and empirical evidence for interventions aimed at prolonged grief disorder after suicide is still lacking [18]. McDaid and colleagues [19], in their systematic review, point to the lack of methodological quality of these studies, and thus, a lack of evidence-based interventions. The thin empirical evidence available, however, suggests that (cognitive-behavioral) interventions might be effective for the reduction of maladaptive grief reactions and the perceived responsibility for suicide [20], the reduction of anxiety and depression in suicidal children [21], and the reduction of suicide-associated grief and depression [22]. In summary, there is a great need for evidence-based psychological interventions for suicide survivors.

### Internet-based bereavement intervention

In recent years, internet-based psychological support has been established in social media for bereaved populations, including online support groups (e.g. Facebook), memorial websites and discussion forums. Parallel to the use of social media, web-based interventions for different types of losses have been developed and evaluated in recent years. These Internet-based bereavement interventions were aimed at bereaved people in general [23–26] or specific groups of bereaved people such as parents who have experienced loss of pregnancy [27, 28]. The treatment effects of Internet-based interventions for grief symptoms were moderate to large, and could be maintained over time [29]. The largest and most robust effects, however, were on grief-related symptoms of PTSD. Most Internet-based bereavement interventions included writing assignments, ranging from extensive structured writing assignments to online diaries and homework assignments, and were based in an individual setting.

Unfortunately, even though they are a high-risk group, suicide survivors are precisely the group that is least likely to seek professional help. A study from the UK showed that suicide survivors in particular were less likely to receive formal (e.g. psychotherapists, doctors) or informal support (e.g. friends, religious counseling), and only every fourth interviewed person made use of any form of support at all. Reasons for the low use of professional psychological support include, for example, a lack of psychosocial care or fear of stigmatization (Pitman et al., 2016b; Pitman et al., 2017). Therefore, the anonymity of the Internet might support bereaved patients in overcoming their initial shame or perceived feelings of stigma, which might prevent them from looking for support. Another advantage of Internet-based intervention is that these interventions offer geographic independence and widespread dissemination of the offer of treatment. This is of particular interest for people living in remote areas without any access to local bereavement groups or specialized grief counsellors. Further, Internet-based interventions provide a more user-friendly and flexible approach that is more responsive to a mobile and digitalized society.

The aim of this study is to develop and evaluate a manualized, CBT-based, online, group intervention after suicide bereavement, using webinars. Previous Internet-based bereavement interventions were almost always writing interventions based on an individual setting. Contrarily, we chose the novel format of a webinar to provide real-time simultaneous interaction between the therapists and the group participants. Grief group interventions can provide unique therapeutic elements such as universality of the suffering, group cohesiveness, role model learning, and interpersonal learning [30, 31]. So far, studies of online group interventions have taken place mainly via videoconferencing. Backhaus and colleagues [32], in their systematic review of videoconferences in psychotherapy, included seven studies altogether that used the group format. The results indicated similar clinical outcomes such as face-to-face interventions. Webinars are, next to videoconferencing, most similar to traditional group interventions for people bereaved by suicide. Webinars provide the possibility to participate in group sessions from a remote location in real time but have the additional advantage of providing the possibility of showing videos and psycho-educative PowerPoint presentations, as is customary in e-learning environments.

### Objectives

The main objective of this trial and the proposed online-group intervention is to reduce depression and suicidality in people bereaved by suicide. Secondary outcomes of the trial are prolonged grief disorder, posttraumatic stress disorder, anxiety, stigmatization, posttraumatic grief cognitions and social support. More precisely, our treatment-specific objectives are to determine whether:
The online group intervention significantly reduces symptoms of depression, suicidality, prolonged grief disorder, posttraumatic stress disorder, and anxiety after bereavement through suicide.The treatment effects (symptom reduction of primary and secondary outcomes) of the online group intervention are significantly greater than those of the control group after the end of treatment.

In addition, the study addresses the following process-specific research questions:
Which factors (such as age, sex, depression, severity of symptoms) are most likely to predict the effect of the treatment?To which extent does the relationship with the deceased (e.g. spouse, sibling, child, parent, friend) influence treatment outcomes in terms of grief and trauma symptoms?Which cognitive processes (such as stigma experience, guilt) influence the general psychopathology of study participants (e.g. depression, prolonged grief, trauma symptoms)?

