### Trial design

This study is a randomized control group design with two groups of equal sample size: the treatment group and the waitlist control group. The treatment group will receive treatment through the online group intervention immediately after registration. As a result of the focus groups with suicide survivors, the waitlist control condition was selected as the only one acceptable to the suicide survivors involved. A control that would not receive the intervention after the waiting period could reduce the motivation to participate.

This intervention is based on cognitive behavioral principles (psychoeducation, cognitive restructuring, dealing with difficult emotions such as guilt, shame, suicidality) and will take place once a week over a course of 12 weeks in total. The waitlist control group will receive the same intervention 12 weeks after registration. Participants will be randomly assigned to either group using computer-generated block-randomization. The study protocol was written in accordance with Statement Standard Protocol Items: Recommendations for Interventional Trials (SPIRIT) 2013 [33]; for the SPIRIT Checklist see Additional file 1).

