### Measures

#### Screening for eligibility criteria

The study coordinators will screen the participants for eligibility criteria using a semi-standardized clinical telephone interview. To exclude the presence of a current major depressive or manic episode, bipolar disorder, BPD, PTSD, or alcohol and substance misuse, the corresponding sections from the German version of the Structured Clinical Interview for DSM-IV [37] will be applied. The inter-rater reliabilities of the diagnoses vary between fair (e.g. agoraphobia) and excellent (e.g. PTSD, BPD) scores [38]. In addition, the German translations [39] of the Dutch Screening Device for Psychotic Disorder [40] and the Suicide Risk Assessment Interview [41] will be used to screen for acute schizophrenia and suicidality, respectively. All outcomes will be aggregated using sum scores, means, or standardized mean differences (i.e., Cohen’s *d* value for effect size) from baseline to post intervention and follow up. Thus, the timeframe will be 12 weeks from pre to post intervention, 3 months from pre to follow-up 1 and 3 months from pre to follow-up 2. The description of the specific outcome information (i.e. domain, measurement) can be found below.

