### Statistical analysis

We will use repeated measures analysis of variance (ANOVA) to analyze the changes in the primary endpoint variables (suicidality and depression) and the secondary outcomes from baseline to post-measurement and the two follow-up assessments (3 months, 6 months), where the dependent variable will be the treatment condition (treatment group vs. waitlist control group). In addition, we will control for the baseline levels of depression and suicidality using analysis of covariance (ANCOVA). The predictor analyses will be conducted using the method of multiple regression. Interim analyses will be calculated to present first results before the study is finished. To control for differences between the online groups, multilevel analyses will be conducted to allow for variation between participants and online groups at level 1. The assignment to the study group (i.e., treatment, wait list) will be on level 2. Intraclass correlation will be tested to examine potential clustering effects of the online groups.

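### Objective 1 names no comparator, so as worded it could be declared met from improvement within the treated arm alone

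*Protocol article*

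**What the plan says.** The Objectives section of the protocol article lists two treatment-specific objectives. The first is to establish whether "The online group intervention significantly reduces symptoms of depression, suicidality, prolonged grief disorder, posttraumatic stress disorder, and anxiety". The second concerns the comparison. It speaks of "The treatment effects (symptom reduction of primary and secondary outcomes"), which equates a treatment effect with a fall in symptoms. It then asks whether these effects "of the online group intervention are significantly greater than those of the control group after the end of treatment", which places the comparison with the waitlist at the close of treatment.

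Under Screening for eligibility criteria, the outcome metrics include "standardized mean differences (i.e., Cohen’s *d* value for effect size) from baseline to post intervention and follow up".

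The Statistical analysis section plans repeated measures ANOVA over baseline, post-measurement and both follow-ups, "where the dependent variable will be the treatment condition (treatment group vs. waitlist control group"). (The word dependent presumably stands for the grouping factor.) It adds ANCOVA for baseline depression and suicidality, and multilevel models with study group at level 2. It does not link either objective to a particular test.

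The Primary outcomes section sets suicidality and depression at post treatment, 3 months and 6 months. On the control arm, Trial design says: "The waitlist control group will receive the same intervention 12 weeks after registration".

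**The concern.** Because the comparison with the control group has an objective of its own, Objective 1 would largely duplicate it if it were also a between-arm statement. The natural reading is therefore change from baseline in the treated arm, stated in causal terms. Equating treatment effect with symptom reduction supports this reading.

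Symptoms in a treated arm can fall for reasons other than the intervention, such as the natural course of grief or other help. The section on monitoring, ethics and safety allows participants to use psychotherapy alongside the study, and the Discussion concedes that such support might affect the effect sizes. With two objectives of equal standing, a significant Objective 1 beside a null Objective 2 would let the report say that the intervention significantly reduces symptoms. A reader would take that as a finding of efficacy from a randomized trial.

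**Working it through.** The protocol states no expected change in untreated people, so there is no figure of its own to reproduce here. The check asks how often Objective 1, read as a within-arm test, would be met if the intervention did nothing.

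**Inputs from the protocol (Sample size; Handling of missing data).** 52 per arm, two-sided alpha 0.05, 30% dropout, last observation carried forward. Dropouts: 52 × 0.30 = 15.6, taken as 16, which leaves 36 completers. The 52 is used as stated; whether it follows from the power inputs is a separate matter.

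**Assumptions (not in the protocol).** Zero treatment effect; recovery d of 0.2, 0.3 or 0.4 baseline SD over 12 weeks in both arms; pre-post correlation r = 0.6, with 0.5 to 0.7 as a range; equal SD at both times; independent participants.

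**Formula.** The SD of change, in baseline SD units, is √(2(1 − r)) = √0.8 = 0.894. The standardized change is dz = d / 0.894, and the noncentrality of the paired t-test is dz × √n.

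| d | dz | dz × √36 | Probability significant, 36 completers | dz × √52 | Probability significant, 52 with no dropout |
|---|---|---|---|---|---|
| 0.2 | 0.224 | 1.34 | 0.257 | 1.61 | 0.353 |
| 0.3 | 0.335 | 2.01 | 0.499 | 2.42 | 0.660 |
| 0.4 | 0.447 | 2.68 | 0.742 | 3.22 | 0.886 |

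**With the planned handling of missing data.** All 52 are analysed, and the 16 dropouts carry their baseline value forward, so their change is zero. Mean change shrinks to 36/52 = 0.69 of d. Simulation gives about 0.26, 0.50 and 0.74 for 0.2, 0.3 and 0.4 SD, practically the same as for 36 completers.

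**Sensitivity to r.** For 36 completers, r from 0.5 to 0.7 gives 0.215 to 0.325 (0.2 SD), 0.417 to 0.618 (0.3 SD) and 0.646 to 0.854 (0.4 SD).

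**Between-arm test on the same data.** In 20,000 simulated trials per scenario without dropout, a two-sample test of change was significant in 0.048 to 0.051 of trials for recovery of 0.2, 0.3 and 0.5 SD. With equal dropout carried forward in both arms (40,000 trials, 0.2 to 0.4 SD) it was 0.042 to 0.050. Recovery common to both arms cancels. This figure treats participants as independent; the effect of assigning whole groups of ten is a different question.

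**Follow-up.** The waitlist receives the intervention from 12 weeks after registration. The 3- and 6-month assessments come after that, so both arms have by then been offered treatment. The ANOVA still compares the arms at these times, but neither arm is untreated.

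**The case against.** The strongest reply is that no within-arm test is planned. Every outcome model in the Statistical analysis section carries the treatment-versus-waitlist contrast, and the paired test used above appears nowhere in the protocol. Objective 1 could be a general statement of aim, with Objective 2 saying how it is judged. The passage on effect sizes from baseline describes metrics and time frames; it is not limited to the treated arm and states no hypothesis. This stands, and it confines the point to the objective and what may be claimed from it. It does not remove the point, because nothing in the protocol says that Objective 1 is judged against the waitlist.

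The recovery sizes are also assumptions. The Background describes impairment that is often lifelong. The eligibility criteria set no minimum symptom score and exclude BDI-II scores above 35, so the usual selection of high scorers who then regress downward is weak or absent. This also stands: the percentages illustrate the exposure and do not forecast it.

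A reader might infer that within-arm change is all that can be reported at 3 and 6 months. The protocol does not support that, since it analyses all time points by condition; what is missing there is an untreated comparator. A reader might also quote the 0.66 and 0.89 from the table as the risk at 0.3 and 0.4 SD. Those figures require complete follow-up of 52, whereas the protocol plans for 30% dropout.

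**Conclusion.** The point holds as a flaw in the wording of Objective 1 and in the conclusions it would license. The randomized contrast at 12 weeks is present in Objective 2 and in the planned models, and this point does not call it into question. If Objective 1 were judged by change in the treated arm, an inert intervention would meet it in about 26%, 50% and 74% of trials under assumed recovery of 0.2, 0.3 and 0.4 SD, with r = 0.6 and 30% dropout carried forward from baseline. A between-arm test would be significant in about 5%. The within-arm figures depend entirely on the assumed recovery and correlation; with no recovery at all they return to 5%.

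**What to change.** Either merge Objective 1 into Objective 2, as a between-arm difference at the end of treatment, or reword it as describing change within the intervention arm, with no claim of effect. Add to the Statistical analysis section that efficacy claims rest on the between-arm contrast at T12, measured before the waitlist is treated, and that within-arm effect sizes are descriptive. Report the 3- and 6-month results as maintenance data without an untreated comparator, and say so wherever they are listed as primary time points.

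This takes a few sentences in the objectives, outcomes and analysis sections. Design, sample size and data collection are unchanged. The price is that fewer positive claims are available: improvement in the treated arm could no longer stand as a finding of efficacy when the comparison with the waitlist is null.

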### Trial design

This study is a randomized control group design with two groups of equal sample size: the treatment group and the waitlist control group. The treatment group will receive treatment through the online group intervention immediately after registration. As a result of the focus groups with suicide survivors, the waitlist control condition was selected as the only one acceptable to the suicide survivors involved. A control that would not receive the intervention after the waiting period could reduce the motivation to participate.

This intervention is based on cognitive behavioral principles (psychoeducation, cognitive restructuring, dealing with difficult emotions such as guilt, shame, suicidality) and will take place once a week over a course of 12 weeks in total. The waitlist control group will receive the same intervention 12 weeks after registration. Participants will be randomly assigned to either group using computer-generated block-randomization. The study protocol was written in accordance with Statement Standard Protocol Items: Recommendations for Interventional Trials (SPIRIT) 2013 [33]; for the SPIRIT Checklist see Additional file 1).

